# Lumen-apposing metal stents (LAMS) versus plastic stents for EUS-guided drainage of walled-off necrosis (WON) (LVPWON): study protocol for a multicenter randomized controlled trial

**DOI:** 10.1186/s13063-018-2901-3

**Published:** 2018-10-11

**Keywords:** LAMS, DPPS, WON, Trial, EUS

## Abstract

**Background:**

Endoscopic ultrasonography (EUS)-guided drainage has become the first-line therapy for late peri-pancreatic fluid collection (PFC). Double pigtail plastic stents (DPPS) and lumen-apposing metal stents (LAMS) are commonly used for PFC drainage. Recently, a multi-institutional consensus on PFC drainage has recommended that LAMS should be the standard care for patients with walled-off necrosis (WON). However, given the poor quality of evidence, we aim to perform a large-scale randomized controlled trial to determine whether LAMS is superior to DPPS for WON drainage.

**Methods/design:**

The study is an open-label, prospective, parallel-group, superiority, multicenter randomized controlled trial. Two hundred and fifty-six patients with WON who will attend 18 tertiary hospitals in China will be randomly allocated to the LAMS or DPPS group before the procedure. The primary endpoint is the clinical success at one month after drainage (reduction in the size of WON to < 2 cm). Secondary endpoints include technical success, operation time, recurrence, adverse events, and secondary interventions.

**Discussion:**

The LVPWON trial is designed to determine whether LAMS is effective, safe, and superior to DPPS for WON drainage.

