## Background

Walled-off necrosis (WON) is a type of pancreatic fluid collection (PFC) that develops in the setting of acute or chronic pancreatitis, trauma, or pancreatic duct obstruction [1]. WON, a delayed complication of necrotizing pancreatitis usually occurring > 4 weeks following the onset of pancreatitis, is PFC surrounded by a radiologically identifiable capsule containing both solid and liquid components [1]. Most WONs are asymptomatic and resolve spontaneously. However, drainage is necessary when it becomes symptomatic or infected, or increases in size over the course of the illness.

In the past decade, the treatment of symptomatic WON has evolved from surgical to endoscopic necrosectomy. Endoscopic treatment has a reduced proinflammatory response compared to surgery for the treatment of WONs [2]. It is associated with lower rates of pancreatic fistula formation and shorter hospital stays [3, 4]. Endoscopic ultrasonography (EUS)-guided drainage has high technical and clinical success and is associated with low adverse events (AEs) making it the optimal drainage approach for WONs [5, 6].

Double pigtail plastic stents (DPPS) is the standard choice for pancreatic pseudocyst drainage with > 90% technical and clinical success rates [5]. DPPS has also been used for WON drainage [7]. Recently, a novel lumen-apposing metal stent (LAMS) with a larger luminal diameter (≥ 10 mm) has been successfully used for EUS-guided drainage of PFC [8]. A multi-institutional consensus made by 22 expert endosonographers recommended that LAMS should be the standard of care for WON drainage [9].

However, the safety of LAMS is still controversial. Some studies have reported that LAMS is superior to DPPS in terms of overall treatment efficacy (90% vs 81%) and a significantly lower number of procedures (2.2 vs 3.6) [10]. LAMS includes single-step deployment and has an anti-migration structure [11, 12]. Other studies have proposed that LAMS was associated with a significantly higher rate of bleeding compared with DPPS [13–15]. Moreover, high quality of evidence with regards to the efficacy and safety of LAMS for WON drainage in Chinese patients is lacking. Given the recent widespread use of LAMS in the management of WON, we designed this open-label, prospective, parallel-group, superiority, multi-center randomized controlled trial (RCT) to investigate whether LAMS is superior to DPPS for WON drainage.

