##### Statistical analysis plan

Categorical data will be described using frequency and composition ratios. Continuous data will be described using mean, standard deviation, maximum, minimum, and median, as well as 25th and 75th quantiles. Baseline demographic analysis based on the descriptive analysis, the likelihood ratio χ2 test will be used for the comparison between the categorical data groups. Fisher’s exact probability method will be used when theoretical frequency of cells exceeding 25% is < 5. Normally distributed continuous datasets will be compared using a group *t*-test. For non-normally distributed continuous data, Wilcoxon rank sum test will be used for comparison between groups. This is a multi-center study. The test conditions of each center are not identical (such as operators, etc.) and the outcomes may be different. For the primary outcome, comparison between groups will be performed using the CMH (Cochran–Mantel–Haensel) χ2 analysis to adjust for the central effect. The differences between the success rates of the groups and their 95% confidence intervals (CI) will also be estimated. AEs will be described by the number and incidence of AEs; the likelihood ratios between groups will be compared using the χ2 test or Fisher’s exact probability test. Major investigators will have access to the final trial dataset and the statistician involved will be blinded to the treatment assignments. Statistical analysis will be performed with two-sided tests at a level of significance of 0.05 (except where specified). Data analysis will be conducted using SAS^®^9.4 statistical software.

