## Discussion

The LVPWON trial has been designed to answer the question of whether LAMS is superior to DPPS for EUS-guided drainage of WON with regards to the clinical success rate and the incidence of AEs. We also want to prospectively investigate the risk factors for success of treatment and complications of EUS-guided drainage, which will provide a reference for the clinical treatment of WON.

EUS-guided drainage has been maturely applied in late PFC with well-defined inflammatory walls [7, 16–18]. Stents used for drainage are diverse. DPPS used in the management of PFC was first reported in the 1980s [19]. Subsequently, self-expanding metal stents (SEMS) and double-flanged LAMS have become the most popular drainage stents for PFC [8, 11, 12].

Due to their small diameter, several DPPSs are needed to achieve adequate drainage of a WON. Metal stents that have a larger diameter are theoretically considered superior to DPPS as they allow for the possibility of WON debridement. A previous study directly comparing DPPS and LAMS demonstrated that the latter had a success rate of 90%, which was higher than the former, and a significantly fewer number of procedures were required with LAMS for WON resolution [10]. In terms of AEs, stent occlusion seems more likely to occur in WON treated with DPPS [10]. Furthermore, new technology associated with LAMS enhance the drainage effect [20]. The procedure of LAMS deployment has become much easier and more economical.

However, with the increasing use of LAMS for WON drainage, LAMS-related bleeding has been more frequently reported [13–15]. In combined endoscopic and percutaneous drainage for symptomatic WON, LAMS did not reduce the time to percutaneous drain removal and was not associated with fewer AEs [21]. Furthermore, LAMS is substantially more expensive than DPPS.

Recently, a consensus guideline formulated by the Asian EUS group RAND/UCLA expert panel raised the issue of stent selection [5]. There are currently no randomized data addressing how LAMS compare with DPPS for WON drainage. An ongoing RCT observed serious LAMS-related AEs, including delayed bleeding in 50% of patients (6/12), buried stent syndrome, and biliary stricture [14]. However, our team had analyzed our center’s experience and determined that the use of LAMS is safe [22].

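### The stated aim is to determine whether LAMS is safe, but adverse events get only a difference test without an interval, and a non-significant result from it could not support that conclusion

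*Protocol article*

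**What the plan says.** **Aim.** The Discussion paragraph of the abstract says: "The LVPWON trial is designed to determine whether LAMS is effective, safe, and superior to DPPS for WON drainage". The Design section gives the same aim, again with safety in it. The main Discussion extends the superiority question to AEs: "whether LAMS is superior to DPPS for EUS-guided drainage of WON with regards to the clinical success rate and the incidence of AEs".

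**The open safety issue.** Background reports possible harm: "Other studies have proposed that LAMS was associated with a significantly higher rate of bleeding compared with DPPS". The main Discussion returns to LAMS-related bleeding and cites an ongoing trial with delayed bleeding in 6 of 12 patients.

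**AE analysis.** The Statistical analysis plan section says "AEs will be described by the number and incidence of AEs" and that "the likelihood ratios between groups will be compared using the χ2 test", with Fisher's exact test as the alternative. The default for all testing is "Statistical analysis will be performed with two-sided tests at a level of significance of 0.05". The same section commits to a 95% confidence interval for the difference in success rates. Its AE sentence has no interval.

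**Sizing.** The Sample size section rests on clinical success alone: 90% versus 75%, 128 per arm including 10% dropout.

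**The concern.** The aim and the analysis do not meet at the word *safe*. A difference test can show that two AE rates differ. When it fails to reject, it does not show that an excess has been ruled out. What a safety statement needs is how large an excess on LAMS the data still allow, which is the upper end of an interval for the risk difference. The section plans that quantity for efficacy but not for AEs, although possible extra bleeding is the safety question that the protocol itself raises.

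At stake is a headline conclusion. The trial could show superiority on clinical success, find bleeding not significantly different, and have no stated analysis that supports or limits the safety part of its aim.

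**Working it through.** **1. Reproduce the protocol's figure.** Inputs from the Sample size section: success 0.90 and 0.75, one-sided alpha 0.025, power 85%, dropout 10%.

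n = [1.960·√(2·0.825·0.175) + 1.036·√(0.90·0.10 + 0.75·0.25)]² / 0.15² = [1.960·0.5374 + 1.036·0.5268]² / 0.0225 = 113.7, so 114 per arm. 114/0.90 gives 127 per arm, or 254 in total, within 2 patients of the stated 256. The sample size is sound for clinical success. It carries no AE assumption.

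**2. Inputs for the AE check.**
- Evaluable patients: 128 less 10% = 115 per arm, with 128 per arm shown as the upper case.
- Test: two-sided 0.05. I read the AE sentence as a likelihood-ratio chi-square test or Fisher's exact test.
- Bleeding rates: the protocol gives no DPPS rate, so 5% and 10% are assumptions.

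**3. Power of the AE test.** Normal approximation: power = Φ{[d·√n − 1.960·√(2p̄(1−p̄))] / √(p₁(1−p₁)+p₂(1−p₂))}.

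For 5% versus 10% at n = 115: (0.05·10.724 − 1.960·0.3725)/0.3708 = −0.52, and Φ(−0.52) = 0.30.

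| DPPS vs LAMS bleeding | Approximation, n = 115 | Fisher / likelihood-ratio (exact enumeration), n = 115 | Fisher / likelihood-ratio, n = 128 |
|---|---|---|---|
| 5% vs 10% | 30% | 21% / 32% | 24% / 35% |
| 5% vs 15% | 72% | 65% / 75% | 71% / 79% |
| 10% vs 20% | 57% | 50% / 58% | 55% / 63% |
| 10% vs 30% | 97% | 96% / 98% | 98% / 99% |

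**4. What a non-significant result leaves open.** Newcombe 95% intervals for LAMS minus DPPS, 115 per arm:
- 12 vs 6 bleeds: 10.4% − 5.2% = +5.2 points, interval −2.0 to +12.7; likelihood-ratio p = 0.14, Fisher p = 0.22.
- 14 vs 6 bleeds, the most that stays non-significant by the likelihood-ratio test (p = 0.058): +7.0 points, upper limit +14.7.
- 6 vs 6 bleeds: difference 0, upper limit +6.4.

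All three results are non-significant, yet their upper limits run from +6.4 to +14.7 points. The p-value alone does not convey that range; the interval does.

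**The case against.** The strongest reply has four parts.

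**No rule equates non-significance with safety.** A reader might infer that a p-value above 0.05 will be reported as proof that LAMS is safe. The protocol does not say so: it gives no definition of safe, no margin and no such decision rule. Following it yields AE numbers, incidences and a p-value. This stands, and the point is limited to what the planned test could support.

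**The test fits one of the questions asked.** A two-sided difference test is suitable for the Discussion's question of superiority on AE incidence, and it can also detect harm. A reader might call that a mismatch too, but it is not. The mismatch concerns only the safety wording in the abstract and the Design section. The closing paragraph of the Discussion already speaks of comparing efficacy and safety, which is close to the wording proposed here.

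**Sizing on the primary endpoint is normal, and the power figures rest on assumed rates.** Both are true. A tripling from 10% would be found with about 97% power, and an excess as large as 50% versus 5% almost surely. It would be wrong to say that the trial could miss any large excess. The gap concerns doublings, and some triplings from a low base.

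**An AE interval may be in a fuller document, or be derived from the reported counts.** This stands only in part. The article does not leave the AE method open: it states the comparison as a test, in the section where it commits to an interval for efficacy. An interval that a reader works out afterwards is not the planned basis for a conclusion.

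**Conclusion.** The concern holds in a limited form. The protocol says it will determine whether LAMS is safe, but the AE comparison it states cannot support that conclusion when the result is non-significant. If bleeding on DPPS is about 5% (assumed), a doubling would be missed about 70% of the time at 115 per arm, and a tripling a little over a quarter of the time. From an assumed 10%, a doubling would be missed about 43% of the time and a tripling about 3%. Using all 128 per arm changes little.

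This is a minor to moderate point about the wording of the aim and the reporting of AEs. The sample size, the primary analysis and the use of a two-sided AE test are not at fault.

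**What to change.** **Statistical analysis plan section:** make the AE result the LAMS-minus-DPPS risk difference with its 95% confidence interval, for bleeding and for any stent-related AE, beside the test already planned. State that safety conclusions rest on that interval, and not on the absence of significance.

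**Abstract and Design section:** word the aim as superiority in one-month clinical success, and estimation of the difference in AEs between LAMS and DPPS.

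**Cost:** a few sentences and two intervals from data already collected. The downside is a more modest safety claim.

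The alternative is to keep a determination of safety as an aim, which would need a pre-specified and justified margin. The protocol has none, and the choice is not made here. The numbers show why estimation is the proportionate route. With equal true rates, one-sided 0.025 and 80% power, n per arm = 2p(1−p)(1.960+0.842)²/margin². At an assumed 5% bleeding rate this is 299 per arm for a 5-point margin and 75 for a 10-point margin. At 10% it is 566 and 142.

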**Trial registration:**

ClinicalTrials.gov, NCT03027895. Registered on 14 January 2017.

**Electronic supplementary material:**

The online version of this article (10.1186/s13063-018-2901-3) contains supplementary material, which is available to authorized users.

## Background

Walled-off necrosis (WON) is a type of pancreatic fluid collection (PFC) that develops in the setting of acute or chronic pancreatitis, trauma, or pancreatic duct obstruction [1]. WON, a delayed complication of necrotizing pancreatitis usually occurring > 4 weeks following the onset of pancreatitis, is PFC surrounded by a radiologically identifiable capsule containing both solid and liquid components [1]. Most WONs are asymptomatic and resolve spontaneously. However, drainage is necessary when it becomes symptomatic or infected, or increases in size over the course of the illness.

In the past decade, the treatment of symptomatic WON has evolved from surgical to endoscopic necrosectomy. Endoscopic treatment has a reduced proinflammatory response compared to surgery for the treatment of WONs [2]. It is associated with lower rates of pancreatic fistula formation and shorter hospital stays [3, 4]. Endoscopic ultrasonography (EUS)-guided drainage has high technical and clinical success and is associated with low adverse events (AEs) making it the optimal drainage approach for WONs [5, 6].

Double pigtail plastic stents (DPPS) is the standard choice for pancreatic pseudocyst drainage with > 90% technical and clinical success rates [5]. DPPS has also been used for WON drainage [7]. Recently, a novel lumen-apposing metal stent (LAMS) with a larger luminal diameter (≥ 10 mm) has been successfully used for EUS-guided drainage of PFC [8]. A multi-institutional consensus made by 22 expert endosonographers recommended that LAMS should be the standard of care for WON drainage [9].

However, the safety of LAMS is still controversial. Some studies have reported that LAMS is superior to DPPS in terms of overall treatment efficacy (90% vs 81%) and a significantly lower number of procedures (2.2 vs 3.6) [10]. LAMS includes single-step deployment and has an anti-migration structure [11, 12]. Other studies have proposed that LAMS was associated with a significantly higher rate of bleeding compared with DPPS [13–15]. Moreover, high quality of evidence with regards to the efficacy and safety of LAMS for WON drainage in Chinese patients is lacking. Given the recent widespread use of LAMS in the management of WON, we designed this open-label, prospective, parallel-group, superiority, multi-center randomized controlled trial (RCT) to investigate whether LAMS is superior to DPPS for WON drainage.

## Methods/design

### Design

The LVPWON trial is an open-label, prospective, parallel-group, superiority, multi-center RCT designed to determine whether LAMS is effective and safe in the EUS-guided drainage of WON and superior to DPPS. Patients with WON admitted at 18 tertiary hospitals in China will be randomly allocated to the LAMS or DPPS group before the procedure. The study protocol has been approved by the Institutional Review Board and Ethics Committee of Shanghai Changhai Hospital. Recommendations for Interventional Trial (SPIRIT) Checklist have been provided (see Additional file 1).

#### Study population

This prospective study will be performed at the National Clinical Research Center for Digestive Diseases and 18 tertiary hospitals in China. All adult patients admitted with WON will be assessed for eligibility during their hospital admission. If patients are found to have solid debris in the PFC and fulfill all inclusion and exclusion criteria, they will be randomized (at a 1:1 ratio) to the LAMS or DPPS group after obtaining signed informed consent (Fig. 1). In this experiment, randomization will be performed using the Interactive Web-Respond System (IWRS).

**Fig. 1 Fig1:**
[figure not shown]
Research *flow chart*

The inclusion and exclusion criteria are listed in Table 1. All patients (aged ≥ 18 years) with WON requiring drainage and fulfilling the inclusion criteria will be eligible for enrollment. Investigators will inform the patients about the trial procedure. Patients will independently choose to participate in the trial and sign the informed consent. Any participant has the right to opt out of this trial at any time. Contraindications for EUS-guided drainage of WON will be determined by endoscopists or anesthesiologists before the procedure. CT images obtained from the 18 hospitals will be uniformly read by Changhai Hospital.

**Table 1 Tab1:** Inclusion and exclusion criteria

Inclusion criteria	
Aged 18–80 years	
Individual with WON confirmed by CT and MRCP	
The size of WON ≥ 6 cm and located adjacent to the gastric wall	
Participants has symptoms related to the WON	
Written informed consent obtained	
Exclusion criteria	
Aged < 18 years or > 80 years	
Individual cannot accept the endoscopic procedure	
The distance between the stomach and the wall of the WON ≥ 1 cm	
Participant has blood coagulation dysfunction (platelet count < 50 × 109/L or INR > 1.5)	
Allergic to nickel titanium	
Suffering from severe lung or heart disease	
Pregnant and lactating women and those who are about to become pregnant soon	
Any other factors that are not suitable for inclusion or influence the individual’s participation in the study judged by researchers	

*WON* walled-off necrosis, *INR* international normalized ratio

#### Treatment protocol

Before the procedure, if an individual meets the inclusion and exclusion criteria, the investigator will report this to the leader unit (Shanghai Changhai Hospital) and the participant will be randomized to receive either LAMS (Fig. 2) or DPPS for WON drainage. Randomization will occur in a 1:1 fashion with a random number table generated by IWRS, making it possible for all patients from different hospitals to be randomly assigned to each group.

**Fig. 2 Fig2:**
[figure not shown]
Lumen-apposing metal stent (Micro-TechCo. Ltd., Nanjing, China)

The operation will be performed under mild sedation, monitored under anesthesia care or under general anesthesia, and prophylactic antibiotics will be used when appropriate. EUS-guided drainage will be performed by expert endosonographers after unified standard operation training. First, the position and size of the WON will be determined by endoscopic ultrasonography and the appropriate puncture point will be selected. Next, a 19G puncture needle will be inserted into the WON via the endoscope. Under fluoroscopy guidance, a 0.035 in. (1 in. = 0.025 m) yellow zebra guide wire will be inserted and coiled into the WON cavity. A Wilson COOK cystotome electric knife will be placed along the guide wire to cut the wall of stomach and the wall of the WON. Balloon expansion will be used if necessary. Subsequently, after drainage of the liquid content of the WON in to the stomach, LAMS or DPPSs would be placed to maintain the opening.

#### Data collection and follow-up

Investigators will save a recording of the operation and note the procedure time. After EUS-guided drainage, patients will be sent back to the ward. Patients will be monitored for 3 h and 24 h serum amylase after the operation and prophylactic antibiotics will be administered postoperatively. Detailed data information can be found in the SPIRIT figure (Fig. 3). After the LAMS is implanted, if the WON needs to be cleaned, direct endoscopic necrosectomy (DEN) will be performed. Stents will be removed one month after implantation. If the clinical success criterion is not met at the one-month follow-up, the patient will be provided with further treatment that will be decided based on their individual needs. All individuals who participated in the trial will be followed up at one, three, and six months post operation, with a final follow-up to occur 12 months after the end of the trial for CT evaluation. The above data will be collected into case report forms (CRFs). Stent-related AEs and management will also be recorded and reported in the CRFs. Finally, CRFs will be summarized by the National Clinical Research Center for Digestive Diseases.

**Fig. 3 Fig3:**
[figure not shown]
Schedule of enrollment, follow-up, and assessments. Basline^0^: screening of laboratory tests can be accepted the previous week in our hospital inspection report. Stent removal^1^: time from stenting to postoperative withdrawal (33 ± 3 days). Blood routine^2^: hemoglobin (HGB), erythrocyte count (RBC), platelet count (PLT), leukocyte count (WBC), neutrophil percentage (%), lymphocyte percentage (%). Liver and kidney function^3^: alanine aminotransferase (ALT), aspartate aminotransferase (AST), total bilirubin, direct bilirubin (DBIL), indirect bilirubin (IBIL), alkaline phosphatase (ALP), glutamyl transferase (GGT), blood urea nitrogen (BUN), creatinine (Cr). Coagulation function^4^: prothrombin time (PT), fibrinogen (FIB), activated partial thromboplastin time (APTT), thrombin time (TT). Serum amylase^5^: assessed 3 h and 24 h after the operation. CT^6^: preoperative and postoperative enhanced CT examination, 3 months and 6 months postoperative CT examination. The primary endpoint^7^: immediate success rate of surgery, drainage success rate 1 month after surgery. Secondary endpoints^8^: the incidence of clinical complications, operation time, the recurrence rate of pancreatic pseudocyst within 1 month and 1 month after the operation, and secondary interventions

